#### Exploratory Study End Point Analyses

Self-reported disease activity (states), worker productivity, sleep, perceived stress, physical activity, and diet compliance are exploratory study parameters.

#### Other Study End Points Analyses

Other study end points are age, sex, disease duration, autoantibody status, presence of erosions, smoking status, and alcohol consumption, which are only compared at baseline. A Student *t* test, chi-square test, or Wilcoxon rank-sum test will be used to compare the difference in aforementioned outcomes, when appropriate.

#### Additional Analyses

Two additional analyses will be conducted to complement the primary analysis. First, we will conduct a complete case analysis that will include all participants who have never missed a study visit. Second, participants with ≥5% weight loss after the intensive part of the lifestyle intervention program will be compared with the complete case in the general nutrition group, because we assume that this weight loss will be associated with the greatest program compliance and thus its possible benefits.

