### Criteria for Discontinuing or Modifying Allocated Interventions

Criteria for discontinuing are as follows:

Pregnancy.Ineligibility (either arising during the trial or retrospectively having been overlooked at screening).An adverse event (AE), which requires discontinuation of the lifestyle intervention or results in the inability to continue to comply with trial procedures.Disease progression, which requires discontinuation of the lifestyle intervention or results in the inability to continue to comply with trial procedures.Withdrawal of consent.Loss to follow-up.

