### Participant Timeline

Patients will be assessed at baseline and after 3, 6, 12, and 24 months. At each visit, patients will fill out online questionnaires (~30 min) and are assessed by the RN, who calculates the DAS28 or DAPSA depending on the diagnosis. Study visits will take 30 minutes or less. The timeline and extensive data collection overview are shown in Figure 2 and Table 2. Data collection is the same for both the intervention group and the control group.

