Disease burden is measured through the following PRO measurements: GH, pain, morning stiffness, fatigue, functional ability, and quality of life. GH, fatigue, and pain are measured with a VAS (0‐100 mm), whereby higher scores reflect greater severity. The MCIDs for the aforementioned outcomes are ≥10 [35-37]. Fatigue is also measured with the Functional Assessment of Chronic Illness Therapy-Fatigue questionnaire (FACIT-F) [38]. The FACIT-F consists of 13-items with a 7-day recall period. Items are scored on a 0‐4 response scale with anchors ranging from “Not at all” to “Very much so.” All items are summed to create a single fatigue score with a range from 0 to 52 and higher scores represent less fatigue [38]. The MCID is 15.9 [39]. Morning stiffness (severity and duration in min) is measured with a Numeric Rating Scale and is interpreted similarly to GH. The MCID for morning stiffness is ≥1 [40]. Functional ability is measured with the Health Assessment Questionnaire [41]. Higher Health Assessment Questionnaire scores indicate poorer function, and the MCID is 0.22 [41,42].

Quality of life is measured with the EQ-5D-5L (MCID ≥0.04) [43,44]. Higher scores represent a higher quality of life. We will also use the 36-item Short-Form Health Survey (SF-36) that assesses 8 domains on a scale of 0‐100, with higher scores indicating a better health status [45]. The SF-36 addresses the following domains: physical functioning, bodily pain, role limitations due to physical health problems and social or emotional problems, mental health, vitality, and GH perceptions. These domains are also combined into a physical and mental component score. The MCIDs for the physical component score and mental component score are 2.5 and 5, respectively [30,45,46].

Although the primary outcome will be assessed after 12 months of follow-up, we will follow all participants for 2 years to determine the long-term effect of the lifestyle intervention and whether the intervention has led to a permanent behavioral change.

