### Sample Size

The HELIA is a superiority trial, powered to detect a 20% difference in DAS28 and DAPSA remission and/or successful tapering of DMARD treatment after 12 months of follow-up. Meeting either criterion is sufficient to qualify for the primary outcome. Murray et al [55] showed that after the first year of diagnosis, remission rates are up to 30%. Although tapering of treatment is still not standard of care, previous research has shown that tapering of treatment in patients with LDA is possible [56]. Based on these data, we assumed that 30% of the patients in the control group, general nutrition recommendations, will reach remission or be able to successfully taper their medication and that this will be 20% higher in patients who will follow the online, interactive lifestyle intervention program. Thus, to detect this 20% difference using a significance level of *α*=.05 (2-sided) and a power of 80%, 100 patients per group (~75 RA and ~25 PsA) are needed, also taking a 10% dropout ratio into account, which is based on previous trials conducted in the Erasmus MC [57,58].

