### Statistical Analysis

#### Overview

Primary and secondary end points are analyzed according to an intention-to-treat principle, also known as full analyses. In an intention-to-treat analysis, all patients are analyzed in the groups to which they were randomized, regardless of whether they received or adhered to the allocated management approach.

Reporting of results will be in accordance with the CONSORT (Consolidated Standards of Reporting Trials) statement. Means (SD) will be presented for normally distributed data and medians (IQR) for nonnormally distributed data. Frequencies are presented as the number of patients (proportion).

We assume that missing data are (missing) at random. Therefore, missing data, in baseline variables as well as in the follow-up data, will be handled with multiple imputations by chained equations, with 40 imputations [59]. A Bonferroni correction will be applied if necessary to account for multiple testing by dividing the *P* value by the number of tests performed. All data analysis, including cleaning, transforming, and modeling, will be done in STATA18 (StataCorp LLC) or higher.

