## Results

Due to administrative issues and time constraints, there has been a delay in registering in the ISCRTN registry. The study protocol was approved on December 6, 2022, by the ethics committee of the Erasmus MC. Patient recruitment began on March 21, 2023, while registration in the ISRCTN (International Standard Randomised Controlled Trial Number) registry was completed on June 13, 2023, which was fully based on the approved protocol by the ethics committee (ISRCTN21290281). Although prospective registration is generally recommended by the ICMJE (International Committee of Medical Journal Editors) guidelines, the authors acknowledge this deviation. They confirm that all study procedures and outcomes were predetermined prior to ethical approval and thus prior to data collection and that the outcomes and analysis plans have not been changed after registration. Recruitment was completed in May 2024. The last visit will take place in May 2026. Subsequently, the data will be analyzed, and the results are expected to be published in 2027.

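### The complete-case set supporting the month-12 primary analysis requires attendance at every visit, so it drops patients whose month-12 outcome was observed, including for a missed month-24 visit (minor)

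*Protocol article*

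**What the plan says.** The Primary End Point and Primary End Point Analyses sections fix the primary outcome at 12 months. It is remission, or tapering without a flare, and either one suffices. The analysis is a covariate-adjusted logistic regression. The Overview of the statistical analysis specifies intention to treat with multiple imputation.

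The Additional Analyses section adds two analyses in support of the primary one.

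- The first has this rule: "First, we will conduct a complete case analysis that will include all participants who have never missed a study visit".
- In the second, intervention patients with at least 5% weight loss after the intensive phase "will be compared with the complete case in the general nutrition group". The first rule therefore also determines the controls here.

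Three other statements determine what a study visit means in that rule.

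- Participant Timeline: "Patients will be assessed at baseline and after 3, 6, 12, and 24 months".
- Secondary End Points: "Although the primary outcome will be assessed after 12 months of follow-up, we will follow all participants for 2 years".
- Results: "The last visit will take place in May 2026. Subsequently, the data will be analyzed". Month-24 attendance will therefore be known when the set is formed.

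Nothing in the Additional Analyses section limits the rule to visits up to month 12.

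**The concern.** A complete-case analysis placed beside an imputed primary analysis should show what the observed month-12 outcomes say without imputation. That requires every patient whose month-12 outcome was observed. Here a patient can be seen at month 12, classified as responder or non-responder, and then removed because of a visit missed a year later. Month 24 carries no information about the month-12 outcome.

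Two things are at stake. Precision is lost, because observed outcomes are discarded. The set is also selected on behaviour after the outcome is known. In an open-label trial, attendance at month 24 could relate to earlier response differently in the two arms. If the complete-case result then differed from the imputed one, a reader could not tell whether missing month-12 data or later attendance was the cause.

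**Working it through.** **Inputs.** From the Sample Size section: 30% response in controls, 20 points more with the intervention (50%), two-sided alpha 0.05, 80% power, 100 per group, "also taking a 10% dropout ratio into account". From Participant Timeline: four follow-up visits. The article gives no rate of missed visits, so every miss rate and attendance rate below is an assumption.

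**Step 1: the plan's own figure.** With unpooled variance, n = (1.960 + 0.842)² × (0.21 + 0.25) / 0.20² = 90.3 per arm, and 90.3 / 0.9 = 100.3. Rounding up at each stage gives 91, then 102. The stated 100 is consistent with this, and the sample size is not in dispute.

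**Step 2: outcomes lost through month 24 alone.** Suppose nobody returns after a missed visit. Then month 24 is the only visit that can exclude a patient seen at month 12. Let m be the proportion missing month 12, and also the proportion of those seen at month 12 who miss month 24. Per 100 randomised, 100(1 − m) are observed at month 12 and 100(1 − m)m of these are lost.

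- m = 2%: 98 observed, 1.96 lost
- m = 5%: 95 observed, 4.75 lost
- m = 10%: 90 observed, 9.0 lost, leaving 81

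**Step 3: precision.** At the design rates, the standard error of the difference in percentage points is 100 × √[(0.25 + 0.21)/n].

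- n = 90 per arm: 7.15
- n = 81 per arm: 7.54

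**Step 4: intermittent misses.** If all four visits are missed independently at rate m, the rule keeps 100(1 − m)⁴ instead of 100(1 − m).

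- m = 2%: keeps 92.2, loses 5.8, of which 1.9 are through month 24 only
- m = 5%: keeps 81.5, loses 13.5, of which 4.3 are through month 24 only
- m = 10%: keeps 65.6, loses 24.4, of which 7.3 are through month 24 only

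The month-24-only share is 100(1 − m)³m. The last line implies that 34.4 per 100 miss at least one visit, far above the 10% dropout allowance, so it is an extreme. The rest of each loss involves a missed month 3 or 6, where some outcomes may not be fully observed (see the objection).

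**Step 5: selection.** Let aR and aN be the month-24 attendance of month-12 responders and non-responders. Among attenders, the odds of response in an arm are multiplied by aR/aN. The odds ratio is therefore multiplied by aR/aN in the intervention arm divided by aR/aN in the control arm. Without selection it is (0.50/0.50)/(0.30/0.70) = 2.33. As an example, take aR = 0.95 and aN = 0.85, so aR/aN = 1.118. An arm without selection attends at 90% throughout.

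- Both arms: 52.8% v 32.4%, difference 20.4 points, odds ratio 2.33
- Intervention arm only: 52.8% v 30.0%, difference 22.8 points, odds ratio 2.61
- Control arm only: 50.0% v 32.4%, difference 17.6 points, odds ratio 2.09

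These are unadjusted odds ratios. The distortion needs a dependence on response that differs between arms. The documents give no evidence that this will occur.

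**The case against.** **The rule may mean visits up to month 12.** The analysis supports a month-12 result, so the authors may have intended only the visits that lead to it. That is possible, and the month-24 reading does rest on combining sections. But month 24 is a scheduled study visit, analysis comes after it, and the text sets no limit. If the narrower meaning was intended, the remedy is the same phrase. Even then, patients with a known month-12 outcome would still be dropped for missing month 3 or 6.

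**Months 3 and 6 can matter to the outcome.** Tapering counts only without a flare, and flare status may draw on the earlier visits. This stands in part. A patient who qualifies only through tapering may not have a fully observed outcome if an earlier visit was missed. Remission at month 12 qualifies without it. A reader might infer that all 5.8 to 24.4 per 100 in Step 4 are observed outcomes thrown away. The flare condition means the documents do not support that. It gives no reason to require month 24.

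**The effect is small, and the bias example is constructed.** Both are true. The attendance rates are illustrative, and equal dependence in both arms leaves the odds ratio unchanged.

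**A reader might go on to fault the missing-data plan as a whole.** The Overview states "We assume that missing data are (missing) at random", and neither additional analysis tests departures from that assumption. This is not a finding here. A condensed article commonly leaves such a sensitivity analysis to the statistical analysis plan, which is not shown, and the article contradicts nothing by stating its assumption.

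**Conclusion.** The point holds and is minor. As worded, the rule excludes patients with an observed month-12 outcome who missed month 24. It also excludes those who missed month 3 or 6 although their month-12 status, including flare status where tapering needs it, is known. The controls in the weight-loss comparison inherit the rule.

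Under assumed month-24 miss rates of 2 to 10% and no intermittent misses, about 2 to 9 observed outcomes per 100 are lost. At 10%, the standard error goes from 7.1 to 7.5 points. Bias in the odds ratio arises only if month-24 attendance depends on response differently by arm.

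A reader might infer that the trial's main result is at risk. It is not: the primary analysis keeps all randomised patients through multiple imputation and does not use this set. What suffers is the value of the supporting analysis as a check.

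**What to change.** Replace the attendance rule in the Additional Analyses section. Complete cases are participants with an observed month-12 primary outcome and observed model covariates, regardless of attendance at other visits. An observed outcome means month-12 remission status and, where classification depends on tapering, tapering with flare status up to month 12. Use the same definition for the controls in the second analysis.

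The cost is one phrase, plus a decision on what counts as known flare status when month 3 or 6 was missed. No patients, visits, data collection or consent are added. The article places analysis after the last visit, so the wording can be settled and dated before analysis begins.

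### The complete-case set for the 12-month endpoint is defined by never missing any visit, which on plain reading includes month 24, so observed primary outcomes are discarded

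*Protocol article*

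**What the plan says.** The Participant Timeline section sets the schedule: "Patients will be assessed at baseline and after 3, 6, 12, and 24 months". The endpoint and the length of follow-up are separated under Secondary End Points: "Although the primary outcome will be assessed after 12 months of follow-up, we will follow all participants for 2 years". On timing, the Results section states: "The last visit will take place in May 2026. Subsequently, the data will be analyzed".

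The Statistical Analysis overview says "We assume that missing data are (missing) at random" and that missing values, at baseline and in follow-up, "will be handled with multiple imputations by chained equations, with 40 imputations".

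The Additional Analyses section then says "Two additional analyses will be conducted to complement the primary analysis". The first is "a complete case analysis that will include all participants who have never missed a study visit". The second takes participants who lost at least 5% of their weight after the intensive phase; these "will be compared with the complete case in the general nutrition group".

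**The concern.** A complete-case analysis normally keeps everyone with the outcome and covariates that the model needs. Here membership depends on attendance at every visit, and nothing in the sentence stops at month 12. Because analysis follows the last visit, month-24 attendance will be known when the set is formed.

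Two things follow. First, observed 12-month outcomes are removed for reasons unrelated to whether the outcome is known. Second, membership depends on an event after the outcome. Whether a patient returns at month 24 may depend on how month 12 went. In a logistic model the odds ratio is distorted if that dependence differs by arm. If it does not differ by arm, the loss is mainly one of precision.

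If this analysis disagreed with the imputed one, a reader could not tell whether the imputation or the attendance filter was responsible. The filter also carries over to the controls in the weight-loss comparison. As written it applies to the controls only, since the weight-loss group is not described as complete cases.

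**Working it through.** **1. The plan's own figure.** Inputs from Sample Size: 30% against 50%, two-sided α = 0.05, power 80%, dropout 10%.

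Unpooled formula: n = (0.30×0.70 + 0.50×0.50) × (1.960 + 0.842)² / 0.20² = 0.46 × 7.849 / 0.04 = 90.3 per arm. Then 90.3 / 0.90 = 100.3, which reproduces the stated 100 per group. The sample size is not in question.

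**2. What the rule requires.**

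| Item | Needed for the 12-month outcome? | Needed for the complete-case set as worded? |
|---|---|---|
| Month 12 visit | Yes | Yes |
| Month 3 and 6 visits | Only possibly, for flare status in patients who qualify by tapering alone | Yes |
| Month 24 visit | No | Yes |

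**3. How many are lost.** The article gives no missingness by visit, so all attendance rates below are assumptions.

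*(a) Dropout alone, total 10% of 200 = 20 patients.* If all leave by month 12, no observed 12-month outcome is discarded. If all leave between months 12 and 24, all 20 are discarded.

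*(b) 10% lost by month 12, then further misses.* Observed at month 12: 90 per arm. Let a be the share of these who miss month 24, and b the share who miss each of months 3 and 6, independently. The number kept per arm is 90 × (1 − a) × (1 − b)². Power uses the pooled two-proportion formula, Φ[(0.20√n − 1.960√(2×0.40×0.60)) / √0.46].

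| a | b | Kept per arm | Discarded in total | Power |
|---|---|---|---|---|
| 0 | 0 | 90.0 | 0 | 78.7% |
| 10% | 0 | 81.0 | 18 | 74.3% |
| 10% | 3% | 76.2 | 28 | 71.6% |
| 15% | 5% | 69.0 | 42 | 67.3% |

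The 78.7% in the first row is slightly below 80% because the pooled formula is stricter than the unpooled one that reproduces the stated size.

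*(c) Equal, independent missingness m at each of four follow-up visits.* The set keeps (1 − m)⁴, against 1 − m observed at month 12.
- m = 5%: 0.815 against 0.95, a difference of 0.135 × 200 = 27.
- m = 8%: 0.716 against 0.92, a difference of 0.204 × 200 = 41.

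Independence spreads misses across different patients. If the same patients miss several visits, fewer are lost. A fair range is therefore 0 to about 40 of 200.

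**The case against.** **The sentence does not mention month 24.** It introduces analyses that support a 12-month result, so the authors may have meant visits up to month 12. That is possible, and the defect is best called an unbounded definition. But the wording, the schedule and the timing of analysis all point to the wider reading, and nothing in the article limits it.

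**Months 3 and 6 may matter.** Under Primary End Point Analyses, a patient can qualify by tapering without a flare, and disease activity is scored at scheduled visits. A missed interim visit could leave flare status unknown for someone who qualifies only that way. This stands, and the fix allows for it. It does not reach patients in remission at month 12, since either criterion suffices, and it gives no reason to require month 24.

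**The consequence is limited.** This stands. The primary analysis keeps every observed outcome. The weight-loss comparison already selects intervention patients on a post-randomisation result, so its control set is not its main weakness.

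A reader might also infer three stronger points that the article does not support:
- *That the missing-at-random assumption goes unexamined.* It cannot be tested from observed data. Neither listed analysis explores departures from it, but such a check may sit in an analysis plan that is not shown, so its absence is no finding.
- *That attendance will differ between arms.* The trial is open-label and only one arm has an intensive programme. However, data collection is the same in both arms and programme sessions are not study visits. A difference is possible but not shown.
- *That a particular number will be lost.* Every count above zero rests on assumed attendance.

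**Conclusion.** The point holds as a badly fixed definition in a supporting analysis. On plain reading, a patient with a known 12-month outcome is excluded for missing month 24, and the same set serves as control group in the second additional analysis.

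The size is uncertain: 0 to about 40 of 200 observed outcomes, with a middle case of about 28 of the 180 observed when 10% are lost by month 12. Power in this analysis would range from 78.7% down to 67.3%. These figures assume the planned 30% and 50% rates, up to 15% of those seen at month 12 missing month 24, and up to 5% missing each of months 3 and 6, independently.

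The primary result is not threatened. What suffers is the value of these two analyses as evidence that it is robust. The correction is worth making because it is cheap, but the matter is modest.

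**What to change.** Define the complete-case set as all randomised patients who meet both conditions:
- the 12-month primary outcome can be classified, meaning remission status at month 12 and, where needed, tapering and flare status up to month 12;
- the covariates of the primary logistic model are observed.

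State that other missed visits do not matter and that month-24 attendance never decides inclusion. Use this set in both additional analyses, on both sides of the weight-loss comparison. The weight-loss group will still need its weight at the end of the intensive phase, by its own definition.

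The cost is a change of wording and one altered selection step, with no new visits. The small downside is that flare status may have to come from medical records when an interim visit was missed; the consent described under Recruitment already covers retrieving necessary record data. Because the Results section says the analysis plans have not changed since registration, the revision should be dated and recorded before group labels are unmasked.

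Optionally, and apart from this finding, a delta-adjusted or reference-based version of the 40 imputations would show how far the result depends on missing at random, if the analysis plan does not already contain one. It would add one table.

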### Interventions

#### Online, Interactive Lifestyle Intervention Program

The online, interactive lifestyle intervention program (Leef! met Reuma) consists of a 6-month, intensive part followed by an 18-month online aftercare period. The online program focuses on 4 pillars, namely nutrition, exercise, relaxation, and sleep. The general principles for each pillar are summarized in Table 1. All principles are explained in more detail during the online plenary sessions (the why and how behind them) through Zoom (Zoom Communications Inc), which can be accessed via a standard web browser. Participants are given tools to implement a healthier lifestyle and to increase their health skills. They are encouraged to implement those changes in ways that fit their daily life. The lifestyle intervention aims for lasting behavior changes (based on the I-Change model) [18]. The guidance team consists of a coach, a dietitian, a program coordinator, and experts on sleep, relaxation, and physical activity. The nutritional advice and diet recommended throughout the course are based on the Dutch Health Council guidelines and existing scientific literature. The diet that is prescribed is comparable to the Mediterranean diet, with an emphasis on unprocessed foods (especially vegetables) and 3 meals a day. Alcohol is excluded from the diet.

Each month, a different pillar is highlighted. Throughout the month, participants are assigned 10 days of daily tasks focused on physical activity, relaxation, or sleep (with the option to extend this period to 28 d). Figure 1 provides a schematic overview of the intervention.

**Table 1. T1:** General principles of Leef! met Reuma.

Pillar	Principles
Nutrition^a^	Eat unprocessed foods and vary in the foods you eat. Eat mostly plant-based. Pay attention to dietary quality and not solely energy content.
Physical activity	Strive to increase your heart rate with moderate-intense physical activity for at least 15‐30 min a day. Implement more physical activity during the day; all physical activity counts. Vary in the type of physical activity you do and find a type of physical activity that suits you and that you can enjoy.
Relaxation	Learn to notice when you are stressed and what causes you to be stressed. Find your personal way to implement relaxation. Control your breathing.
Sleep	Pay special attention to sleep quality and not only to the amount of sleep. Develop your own personal, effective sleep hygiene.

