**Figure 1. F1:**
[figure not shown]
Schematic overview intervention (Leef! met Reuma).

There are 5 online plenary sessions lasting 3 to 4 hours for all participants (50 per group), and each session focuses on 1‐2 pillars. The online sessions start with a presentation with in-depth information about the specific pillar, and throughout the presentation, participants can ask questions. After that, the group is divided into several smaller online coaching groups. In these groups, the coach explains how to implement specific changes into participants’ lifestyles. During these 1-hour coaching sessions, the progress that participants have made will be discussed, but also obstacles, experiences, or situations that participants have encountered. Tips are given to help them stay motivated and keep the lifestyle behavioral changes they have made. One example is that participants will learn how to develop their own recipes according to the nutrition principles of the lifestyle program.

After the first 6 months, participants can participate in facultative sessions to stay motivated and foster the healthier habits they have learned during the intensive part of the program. These facultative sessions are similar to the coaching sessions but also include a recap of the knowledge gained during the first 6 months of the program. A facultative session is organized every 9 weeks. The total duration of these plenary, coaching, and facultative sessions is 16, 7, and 10 hours, respectively.

Throughout the entire program, participants can access the Voeding Leeft online platform to stimulate the implementation of healthier habits. At this platform, there are recipes for 30 days, and participants can also find more background information about all 4 pillars, ask questions (directed at the program coordinator, nutritionist, coach, or peers), chat with other participants to share their experiences and/or track their progress to ensure the implementation of a more lasting lifestyle behavior change.

Noteworthy is the fact that there will be no information exchange between the treating rheumatologist and the organization of the online, interactive lifestyle intervention program. However, for this trial, Voeding Leeft will record whether participants attend the plenary and coaching sessions and track their activity on the online platform.

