### Strategies to Improve Adherence to Interventions

Patients have a personal responsibility for the implementation of the online lifestyle intervention program theory or general nutrition recommendations into their own lives. All food products are available at the local grocery store or butcher, and participants should buy them at their own expense. To measure adherence to the lifestyle program, a questionnaire is included to assess diet compliance. In addition, a sensitivity analysis will be performed on patients who have ≥5% weight loss after the intensive part of the lifestyle intervention program because we assume that this weight loss is associated with program adherence.

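### The ≥5% weight-loss comparison selects one arm on a month-6 outcome, so it is liable to show benefit without any programme effect if weight losers would have done better anyway

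*Protocol article*

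**What the plan says.** Under Additional Analyses, the article plans two analyses to complement the primary one. The first is a "complete case analysis that will include all participants who have never missed a study visit". The second filters the intervention arm: "≥5% weight loss after the intensive part of the lifestyle intervention program will be compared with the complete case in the general nutrition group". The reason given is "because we assume that this weight loss will be associated with the greatest program compliance and thus its possible benefits".

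Strategies to Improve Adherence to Interventions describes the same idea as a sensitivity analysis: "a sensitivity analysis will be performed on patients who have ≥5% weight loss after the intensive part of the lifestyle intervention program". The justification offered there is similar: "we assume that this weight loss is associated with program adherence".

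Other parts of the article bear on this:

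- Weight is one of the health-risk measures under Secondary End Points. Participant Timeline and Table 2 show it measured at the same visits in both arms.
- The Interventions section, after Figure 1, states that "Voeding Leeft will record whether participants attend the plenary and coaching sessions and track their activity on the online platform". A 17-item diet compliance score is also collected (Exploratory End Points).
- Table 1 tells participants "Pay attention to dietary quality and not solely energy content". Neither the inclusion nor the exclusion criteria mention BMI.
- The Statistical Analysis overview makes intention to treat the basis for primary and secondary end points.

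**The concern.** The weight-loss condition applies to the intervention arm alone, although the same weights are measured in controls. It is met or failed about six months after randomisation. Those who meet it may be more motivated, or have milder disease, than those who do not. The comparison sets them against controls among whom the corresponding less successful patients remain. As written, the completeness rules differ too: controls must have attended every visit, while no such rule is stated for the weight-loss group. The article names no adjustment or causal method for this contrast.

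Motivation could reach the end point directly. The trial is open-label, tapering is decided by the rheumatologist together with the patient, and DAS28 and DAPSA both contain patient-rated items.

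Weight loss is also an imperfect marker of adherence here. With no BMI entry criterion, an adherent participant with little weight to lose would count as non-adherent. The programme also covers exercise, relaxation and sleep.

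The label matters because a sensitivity analysis should ask whether the same treatment effect survives changed assumptions. This analysis replaces the randomised contrast with a selected one, so it cannot test the robustness of the primary result. It could nevertheless be read as doing so, especially beside a null primary result.

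**Working it through.** **The plan's own figure.** The Sample Size section gives 30% versus 50%, two-sided α 0.05, power 80% and 10% dropout. With unpooled variance:

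n = (1.96 + 0.842)² × (0.30×0.70 + 0.50×0.50) / 0.20² = 7.85 × 0.46 / 0.04 = 90.3, so 91 per arm.

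90.3 / 0.90 = 100.3. The stated 100 per group is reproduced to rounding, and 100 less 10% leaves 90 evaluable per arm.

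**Inputs for the check**

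- Success rate 30% in both arms (the article's control rate, with no programme effect assumed).
- 90 evaluable per arm (from the line above).
- f, the share of the intervention arm losing ≥5%: assumed 30–50%. The article does not give it.
- OR, the odds ratio for success between weight losers and other patients within the arm, purely prognostic: assumed 1 to 3. The article does not give it.

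**Model.** Let p1 be the success rate in weight losers and p0 the rate in the rest of the intervention arm.

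- f·p1 + (1−f)·p0 = 0.30
- p1/(1−p1) = OR × p0/(1−p0)
- Spurious difference d = p1 − 0.30
- SE = √[p1(1−p1)/(90f) + 0.30×0.70/90]
- Chance of a significant result favouring the programme = 1 − Φ(1.96 − d/SE)

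**Worked case, f = 0.3 and OR = 2.** p1 = 0.406 and p0 = 0.255 (check: 0.3×0.406 + 0.7×0.255 = 0.30). d = 10.6 points. SE = √(0.241/27 + 0.21/90) = 0.106. d/SE = 1.00. The upper tail beyond 1.96 − 1.00 = 0.96 is about 17%.

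| OR | d, f = 0.3 | d, f = 0.5 | False positive, f = 0.3 | False positive, f = 0.5 |
|---|---|---|---|---|
| 1 | 0 | 0 | 2.5% | 2.5% |
| 1.5 | 6.1 | 4.2 | 8.5% | 7.1% |
| 2 | 10.6 | 7.2 | 16.8% | 12.9% |
| 3 | 16.9 | 11.1 | 34.9% | 24.4% |

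(d in percentage points.)

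**Cross-check.** Simulating the same settings with a pooled z-test (200,000 runs each) gives somewhat higher rates in favour of the programme: 8–10% at OR 1.5, 14–19% at OR 2 and 26–39% at OR 3. At OR 1 the two-sided error is about 5%, as it should be.

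**Outside the range.** At f = 0.2 the differences are 7.1, 12.4 and 20.0 points for OR 1.5, 2 and 3. The last equals the effect the trial is powered to detect. For OR below 1, d is negative.

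**Would applying the filter to both arms cure it?** Only if weight loss has the same frequency and prognostic meaning in each arm. If the programme changes who loses weight, the matched subsets are still not a randomised comparison. The as-randomised comparison has expected difference 0 under the null.

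**The case against.** The strongest reply is that this is the second of two additional analyses. The primary end point has its own prespecified logistic model under intention to treat, and its estimate, error rate and sample size are untouched. The link between weight loss and adherence is openly stated as an assumption. All of this stands, and it limits the severity.

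A reader might infer that the comparison must show a benefit, or can only flatter the programme. The documents do not support that. The bias depends on a prognostic link for which they give no figure, and it vanishes at OR 1.

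A reader might also call the controls unselected. They are not: having missed no visit is itself a post-randomisation selection, plausibly towards motivated patients, and could offset part of the bias. The calculation leaves this out by setting controls at 30%. It is also unadjusted; using the primary model's covariates might remove some of the imbalance.

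Nor can the direct adherence data be called unused. Diet compliance is collected to measure adherence and is an exploratory end point, and a fuller analysis plan may use attendance. What can be said is that none of these measures defines this comparison.

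Finally, weight is not irrelevant as a marker. Table 1 does not dismiss energy content, and the pilot reported in the Discussion found a mean loss of 4.2 kg in inflammatory arthritis during the intensive phase. This does not rescue the contrast: even a good marker of adherence, applied to one arm only, compares selected patients with controls not selected in the same way.

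**Conclusion.** The concern holds in this form: the comparison filters one arm on a post-randomisation outcome, randomisation does not protect it, and calling it a sensitivity analysis is wrong. It is liable to favour the programme under no effect, provided weight losers have a better prognosis anyway. That is plausible for a variable chosen as a compliance marker, but the documents do not quantify it.

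For f of 30–50% the artefact is about 4–6 points at OR 1.5, 7–11 at OR 2 and 11–17 at OR 3, against a target effect of 20 points. These sizes rest on the assumed f and OR, 30% success in complete-case controls, 90 per arm and no covariate adjustment. It would be wrong to infer that the primary result is compromised. This should be fixed, but it does not threaten the trial's main conclusion.

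**What to change.** 1. Stop calling the comparison a sensitivity analysis under Strategies to Improve Adherence to Interventions, and stop presenting it under Additional Analyses as complementing the primary analysis.
2. If the weight-loss subset is still reported, label it descriptive and non-randomised, with no P value and no claim of effect.
3. For the adherence question, add a complier average causal effect analysis of the 12-month primary end point. Use randomisation as the instrument, keep all randomised patients, and define adherence from recorded attendance at the 5 plenary and 7 coaching sessions, with the threshold fixed before unmasking.

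**Cost.** Plan wording and modest programming; the article says attendance is being recorded. The last visit is given as May 2026 with analysis afterwards, so the change can precede the analysis. The complier estimate will have a wider interval, and its assumptions must be stated, notably that allocation acts on the outcome only through attendance. It answers a question about attendance, not about behaviour change as such. Because the Results section states that analysis plans have not changed since registration, the change must be documented and dated as a departure from the published plan.
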